**Figure 2 F2:**
[figure not shown]
Data sheet: instrument markings on neonatal head and face.

If the delivery is completed by caesarean section the operator will record the position of the head at delivery. If the position of the fetal head was defined as occipito-anterior but is in an occipito-posterior position at caesarean section the diagnosis of the fetal position will be considered incorrect. This information will be cross-referenced with the instrument markings recorded by the neonatologist in cases where there was an initial attempt at instrumental delivery.

The primary outcome will be validated independently by a single investigator who is not involved in scanning or the delivery by reviewing the trial documents (fetal head position recorded by the obstetrician, diagrammatic records of instruments markings on the neonate and documented position of the head position at delivery as described above). Trial allocation will be concealed from this person. Two additional data items will be recorded; i) where the position has been correctly identified the application of the instrument will be classified as optimal or sub-optimal based on the instrument markings and ii) where there is discordance between the findings of the clinician and ultrasonographer the researcher will record whether the ultrasound finding was accepted or not.

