### Validation study

Prior to starting this study, it was important to compare the accuracy of diagnosis of the fetal head position in the second stage of labour by ultrasound scan performed by a novice sonographer and by clinical assessment, to that of an expert sonographer (gold standard); and to evaluate the acceptability of ultrasound in the second stage of labour to women and clinicians [23]. We recruited sixty women who had: (i) an abdominal scan performed by a novice; (ii) an abdominal scan performed by an expert ultrasonographer; and (iii) a clinical assessment performed by an obstetrician or midwife; in the passive second stage of labour. Each assessor was blinded to the findings of the others. The ultrasound findings of the novice and expert ultrasonographer were consistent in 52 (87%) cases for the fetal head position and the novice made no occipito-anterior/occipito-posterior (OA-OP) errors. The clinical diagnosis of the fetal head position was incorrect in 25 (42%) cases with 8 (13%) OA-OP errors [23]. We used these findings as an estimate of the primary outcome for the power calculation, Women and clinicians did not consider the ultrasound assessment to be intrusive. In summary, we found that an abdominal scan by a novice ultrasonographer is an accurate and acceptable method of diagnosing the fetal head position in the second stage of labour [23].

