### Outcome measures

#### Primary outcome

The primary outcome measure is incorrect diagnosis of the fetal head position. Most errors of clinical diagnosis are where the position is classified as occipito-anterior but is in fact occipito-transverse or occipito-posterior. Incorrect diagnosis of the fetal head position will be established according to any of the following criteria:

i) Position of the head at the time of delivery

If the position of the fetal head was classified as occipito-anterior and is delivered occipito-posterior the diagnosis of the fetal position will be considered incorrect.

ii) Instrument markings on the neonatal head and face

The neonatologist or midwife who attends the delivery will examine the baby. He/she will be asked to record the markings of the instrument on a drawing of the head and lateral aspects of the face (Figure 2). The recorded markings will be used to indicate misplacement of the instrument at a distance from the flexion point (vacuum) or over the face (forceps). If for example the recorded position prior to instrumental delivery was occipito-anterior and the instrument placement suggests an occipito-transverse or occipito-posterior position the diagnosis of the fetal position will be considered incorrect. Furthermore, the diagnosis will be considered incorrect if the markings are more than 45^0^ from the documented fetal head position.

iii) Position at caesarean section

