#### Sample size

The rate of inaccurate diagnosis (difference of more than 45 degrees) was hypothesized to be 20% in the usual care arm (clinical assessment alone) and 10% in the intervention arm (clinical assessment and ultrasound). With 225 women per arm, the study will have 80% power with 5% two-sided alpha, to detect the hypothesized 10% difference. However, it is possible that inaccuracy rates are being under- or over- estimated. It could be argued that any difference in effect on the primary clinical outcome would be worth detecting. Rather, given the need for timely delivery of evidence, we have specified detectable differences for realistic sample sizes recruited within a reasonable time frame within the constraints of the available funding.

The combined annual birth rate for the two recruiting hospitals is 13,500, and around 40% of women will be nulliparous, of whom 30% will have an instrumental delivery. We estimate that there will be a total of 3240 instrumental deliveries among nulliparous women over the 24 month recruitment period based on hospital statistics for 2007. Allowing for 30-50% exclusion and non-consent, 95% collection of the primary outcome, and recruiting for 24 months during office hours yields a conservative estimate of 450 participants (225 per arm) for analysis. This would enable detection of a between-group difference of 10–13 percentage points (odds ratio 0.44 to 0.55) with 80% power and 5% two-sided alpha, and would certainly be considered by women and clinicians as worthwhile. These conservative recruitment estimates take account of eligibility criteria, non-english speaking women and the potential difficulty of randomisation and ultrasound evaluation in the context of suspected “fetal distress”.

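### At a direct caesarean the primary outcome counts only an occipito-anterior call found occipito-posterior, although the trial is sized on any difference of more than 45 degrees

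*Protocol article*

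**What the plan says.** The Sample size section sets the outcome on which the trial is powered: "The rate of inaccurate diagnosis (difference of more than 45 degrees) was hypothesized to be 20% in the usual care arm", against 10% with ultrasound.

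The Primary outcome section says "Incorrect diagnosis of the fetal head position will be established according to any of the following criteria", and lists three:

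- **(i) Position at delivery.** An error is a head classified as occipito-anterior (OA) and delivered occipito-posterior (OP).
- **(ii) Instrument markings.** An OA call with placement suggesting occipito-transverse (OT) or OP is given as an example. A general rule follows: markings more than 45 degrees from the documented position make the diagnosis incorrect.
- **(iii) Position at caesarean.** The operator records the head position, and the diagnosis is incorrect "If the position of the fetal head was defined as occipito-anterior but is in an occipito-posterior position at caesarean section". Where an instrument was tried first, this is cross-referenced with the markings.

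The same section states: "Most errors of clinical diagnosis are where the position is classified as occipito-anterior but is in fact occipito-transverse or occipito-posterior". A single investigator, masked to allocation, validates the outcome from the trial documents.

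**The concern.** Only criterion (ii) carries the 45-degree definition used for sizing, and it needs instrument markings. A woman who goes straight to caesarean has none. For her, three kinds of error meet no criterion: called OA and found OT, called OT and found OP, and called OP and found OA. The protocol itself names the first among the main clinical errors. The information to score all three exists, because the operator records the position.

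Two things are at stake. Errors that the sample size assumes will be counted may be lost, which lowers the event rate and the power. The loss may also differ by arm. The Discussion (Potential and implementation of the findings) expects that accurate diagnosis of a malposition may lead the obstetrician to abandon the procedure for a caesarean, and Secondary outcomes lists direct caesarean as a procedural outcome. The intervention could therefore move women to the route with the weakest ascertainment. In particular, a wrong OP diagnosis prompted by the scan, followed by direct caesarean of an OA head, would not count as an error.

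**Working it through.** **1. The plan's own figure.** The inputs, from Sample size, are 20% vs 10%, two-sided 5% alpha, 80% power and 225 per arm. The two-proportion formula is

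n = [1.96·√(2·0.15·0.85) + 0.8416·√(0.20·0.80 + 0.10·0.90)]² / 0.10² = 199 per arm.

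With continuity correction, n′ = (199/4)·[1 + √(1 + 4/(199·0.10))]² = 219 per arm. Power at 225 per arm is 84.6% uncorrected and 81.3% corrected. The stated 225 is consistent with the corrected formula, which is used below.

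**2. Share of errors an OA-OP rule would miss.** From Validation study: "The clinical diagnosis of the fetal head position was incorrect in 25 (42%) cases with 8 (13%) OA-OP errors". An OA-OP rule captures 8/25 = 32% and misses 17/25 = 68%. The article gives no degree threshold for those 25 errors, so 68% is approximate for errors over 45 degrees. As an alternative assumption, suppose errors over 45 degrees were 20% of the 60 women (12) and included all 8 OA-OP errors. Capture would then be 8/12 = 67% and the missed share 33%.

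**3. Effect on power.** Let c be the share of women with a caesarean and no usable markings. The documents give no value, so c is assumed, and equal in both arms here. Recorded rate = true rate × (1 − 0.68c).

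| c (assumed) | Recorded rates | Power at 225 per arm | n per arm for 80% |
|---|---|---|---|
| 0 | 20.0% vs 10.0% | 81.3% | 219 |
| 2% | 19.7% vs 9.9% | 80.6% | 223 |
| 5% | 19.3% vs 9.7% | 79.5% | 228 |
| 10% | 18.6% vs 9.3% | 77.7% | 238 |

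With a missed share of 33%, c = 10% gives 0.20 × (1 − 0.033) = 19.3% vs 9.7%, practically the 5% row.

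**4. False difference between arms.** Take a true error rate of 20% in both arms, whatever the mode of delivery. Let m be the missed share. False difference = 0.20 × (c_scan·m_scan − c_usual·m_usual).

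- m = 0.68 in both arms: c = 5% usual vs 10% scan gives 0.20 × 0.05 × 0.68 = 0.7 points; 2% vs 10% gives 0.20 × 0.08 × 0.68 = 1.1 points.
- m = 0.33 in both arms: 0.3 and 0.5 points.
- Ceiling, m = 1 in the scan arm and 0.68 in usual care: 0.20 × (0.10 − 0.034) = 1.3 points; 0.20 × (0.10 − 0.0136) = 1.7 points. The basis is that none of the novice's 60 − 52 = 8 disagreements with the expert was an OA-OP error. It is a ceiling because the trial scores the position recorded by the obstetrician, who also examines the woman and may reject the scan.

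**The case against.** The strongest reply is that the gap is narrow. The population is women judged to need an instrumental delivery. Where an instrument is tried and fails, the markings and the cross-reference bring the 45-degree rule to bear. That stands, and it confines the point to direct caesareans and to cases without markings.

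Second, criterion (iii) is written as a sufficient condition. It does not say that other discrepancies are correct, and a masked investigator reviews every recorded position. This helps less. Incorrect diagnosis is established by the listed criteria. Criterion (ii) offers its OA case as an example and adds a general rule, while (i) and (iii) do neither. The article gives the masked investigator no wider rule to apply.

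Third, the Discussion speaks of caesarean after a malposition has been diagnosed accurately. Extra caesareans by that route are in women with no error to miss, so a uniform 20% error rate overstates the bias. This is fair. Caesareans after a wrong OP call remain possible, but the documents give no frequency for them.

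A reader might also infer that women who cannot be assessed are scored as correct by default. The article does not say so. Sample size allows for 95% collection of the primary outcome and counts 450 women for analysis, so some outcomes are expected to be missing. How they are handled may be set out in the full protocol or analysis plan.

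**Conclusion.** The point holds as an inconsistency in the definition of the primary outcome. The Sample size section and criterion (iii) describe different errors, and at a direct caesarean the narrower rule applies although the operator records the position.

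The effect is probably small. If 2% to 10% of women are affected, power is 80.6% to 77.7% instead of 81.3%, and the false difference between arms is 0.3 to 1.1 points, or 1.7 at the ceiling, against a target of 10. These figures rest on assumed caesarean shares, on a missed share taken from 25 errors with no stated degree threshold, and on an error rate unrelated to mode of delivery. A reader could obtain a larger bias by assuming far more caesareans in the scan arm, but nothing in the article supports such shares. That ascertainment differs by arm is a plausible inference from the Discussion, not something the protocol states. The case for change rests on the inconsistency and the low cost of removing it, not on a demonstrated threat to the result.

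**What to change.** Reconcile the Primary outcome criteria with the definition in Sample size:

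1. At caesarean, have the operator mark the head position on the 24-section clock already used for the clinical assessment (Usual care arm, Figure 1). Score an error when it differs by more than 45 degrees, in either direction, from the obstetrician's final recorded position.
2. The one-directional rule in criterion (i) can stay for vaginal birth, where an OP head may have been turned to OA before delivery. Say that this is the reason.
3. Report by arm how many outcomes were assessed by each criterion, so that any difference in ascertainment is visible.

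The cost is a sentence in the outcome definition, one diagram on the caesarean form and one descriptive table. The sample size does not change. The downside is that some head movement between diagnosis and caesarean may be counted as error.

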### Allocation to trial groups

Allocation of eligible women who consent to participate in the trial will be concealed using a fully automated centralised web-based system provided by the Bristol Randomised Trials Collaboration. The randomisation sequence will be created by using block sizes of 4, 8 and 12 and stratified by centre, in a 1:1 ratio for usual care versus intervention.

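### The validator is masked to trial arm, but nothing separates the obstetrician's recorded position from the reading of the instrument markings; a locked two-step read would be a cheap safeguard

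*Protocol article*

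**What the plan says.** The Primary outcome section gives three criteria, and meeting any one makes the diagnosis incorrect: (i) the position at delivery, (ii) the instrument markings on the baby, (iii) the position at caesarean section. Criteria i and iii set one recorded category against another: called occipito-anterior (OA), found occipito-posterior (OP). Criterion ii starts from a drawing made by the neonatologist or midwife at the delivery. Its example is a recorded OA position where "the instrument placement suggests an occipito-transverse or occipito-posterior position the diagnosis of the fetal position will be considered incorrect". It then adds a numerical limit: markings more than 45 degrees from the recorded position.

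The section closes with an independent validation by a single investigator who took no part in scanning or delivery, carried out "by reviewing the trial documents (fetal head position recorded by the obstetrician, diagrammatic records of instruments markings on the neonate and documented position", the last item being how the head lay at birth. The masking is stated in one sentence: "Trial allocation will be concealed from this person". No order of reading is given, and nothing other than allocation is said to be withheld. Where the position was correctly identified, the application is also classed as optimal or sub-optimal from the same markings. The criteria are introduced with the remark that "Most errors of clinical diagnosis are where the position is classified as occipito-anterior but is in fact occipito-transverse or occipito-posterior".

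**The concern.** Masking to arm is not masking to the diagnosis under test. The marking drawing is part of the reference against which the recorded position is judged. A reader who already knows the recorded position may be drawn towards agreeing with it, or may look harder for error when it is OA, because the protocol says most clinical errors lie there. Off-centre marks can be scored as a wrong diagnosis, which is an event, or as a correct diagnosis with a sub-optimal application, which is not. One drawing serves both calls.

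For the same recorded position and the same drawing, a masked reader treats both arms alike. The arms may still supply different inputs. In the intervention arm the obstetrician is told the scan finding before proceeding, so the mix of recorded positions, or of error types, may differ from usual care. A reading error that depends on that mix would then appear as a difference between arms in the primary outcome.

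**Working it through.** **1. The plan's own figure, as a yardstick.** The Sample size section says the error rate "was hypothesized to be 20% in the usual care arm (clinical assessment alone) and 10% in the intervention arm", and "With 225 women per arm, the study will have 80% power with 5% two-sided alpha". Allocation is "in a 1:1 ratio for usual care versus intervention". The 450 for analysis already allows for "95% collection of the primary outcome".

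- Without continuity correction: n = [1.96·√(2·0.15·0.85) + 0.842·√(0.20·0.80 + 0.10·0.90)]² / 0.10² = 199 per arm. With 225 per arm, power is 84.6%.
- With continuity correction: n = (199/4)·[1 + √(1 + 4/(199·0.10))]² = 219 per arm. With 225 per arm, power is 81.3%.

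The stated 225 is reproduced closely with the correction, so the sample size is not in question. The standard error of the difference is √[(0.16 + 0.09)/225] = 0.033, or 3.3 points.

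**2. Where judgement enters.**

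| Element | What is compared | Room for judgement |
|---|---|---|
| Criterion i | Recorded OA against delivered OP | Little |
| Criterion ii | Recorded position against a hand drawing | Yes: position or angle is read off the drawing |
| Criterion iii | Recorded OA against OP at caesarean | Little, apart from cross-reference to the markings |
| Optimal or sub-optimal | Marks against good placement | Yes |

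**3. Over-calling error when OA is recorded.** Artefact = (difference between arms in the share recorded OA) × (extra false-error rate when OA is recorded). Neither figure is in the documents. Assumed ranges are 10 to 20 points and 5 to 10 points:

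- low: 0.10 × 0.05 = 0.005, or 0.5 points
- high: 0.20 × 0.10 = 0.020, or 2.0 points

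That is 5% to 20% of the planned 10-point difference, or 0.15 to 0.6 of one standard error. If more women are recorded OA under usual care, it flatters the scan.

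**4. Anchoring towards agreement.** Suppose true errors are recognised with the same probability s in both arms. At s = 0.8 (assumed) the rates become 16% and 8%. The difference falls to 8 points, the odds ratio moves only from 0.444 to 0.457, and power without correction falls from 84.6% to 74.4%. At s = 0.9 the difference is 9 points and power is 80.0%. This dilutes the effect.

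**5. Could error types differ by arm?** In the Validation study, 8 of 25 clinical errors were OA-OP (32%), against 0 of 8 novice-scan disagreements (60 − 52 = 8). If OA-OP errors are always recognised and smaller ones with probability 0.8 (assumed), recognition is 0.32 + 0.68 × 0.8 = 0.864 under usual care and 0.80 with that scan mix. With equal true rates of 20%, the observed rates would be 17.3% and 16.0%, the odds ratio 0.912, and the two-sided rejection rate 6.5% instead of 5%. This shows only that a reader masked to arm can still produce an arm difference. It depends on the size of the error, which a blind read might also miss, and the intervention arm uses clinical assessment plus scan, so its error mix need not match the scan alone.

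**The case against.** The strongest reply is that the outcome is itself a comparison, so the validator must see the recorded position at some point, and the article lists the documents reviewed without saying they are opened together. The order of reading is operational detail that a full protocol may contain. This stands in part: simultaneous reading is an inference, and nothing in the article rules out a staged read. What the article does state is the set of documents and one form of masking, with no separation between the diagnosis and the marks.

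The scope for judgement is also limited. Criteria i and iii are close to mechanical. Criterion ii has a 45-degree limit, and the recorded position is plotted on a clock of 15-degree sections. That also stands, and it confines the point to criterion ii and the optimal or sub-optimal call.

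A reader might infer that the outcome is biased in favour of the scan. The documents do not support that. They give no misreading rate; over-calling and anchoring push in opposite directions and could cancel; and they do not say how, or whether, the recorded position changes after the scan result is given. The remark about where most errors lie describes clinical diagnosis and does not instruct the validator.

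**Conclusion.** The point holds as a cheap improvement, not as a demonstrated error. As described, the validation masks the reader to arm but does not protect the reading of the markings from knowledge of the recorded position. Criterion ii and the optimal or sub-optimal classification are exposed; criteria i and iii are little affected. The direction of any bias is undetermined, and a difference by arm requires a different mix of recorded positions or error types together with a reading error that depends on it. No size can be stated except under assumption: the 0.5 to 2.0 points rest wholly on the two assumed ranges and are small beside a standard error of 3.3 points. The stronger conclusions, that the comparison is biased or that its false-positive rate is inflated, do not follow from the documents.

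**What to change.** Stage the validation, with the same person and the same documents.

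1. With the recorded diagnosis withheld, the validator reads the marking drawing and enters the offset of the marks in degrees from correct placement, taking the flexion point as reference for vacuum and symmetric placement for forceps. The documented delivery or caesarean position is entered alongside. Both entries are locked.
2. The recorded position is then released, and the stated OA/OP and more-than-45-degree rules are applied mechanically.

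The first step should record an offset only, not a position inferred from the marks alone. Marks show where the instrument lay on the head, and a well-centred application could look the same for a correctly diagnosed OA or OP head.

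The cost is a change in the order of document release, a locked entry on the validation form and slightly more handling time per case; no extra staff are needed. If the full protocol already sets such an order, one sentence saying so settles the point. The change does not address any influence on the attending staff who draw the marks.

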#### Secondary outcomes

Secondary neonatal outcomes will include trauma, low Apgar scores, low arterial blood gases and admission to the neonatal intensive care unit (NICU). Neonatal trauma will include bruising, laceration, cephalhaematoma, retinal haemorrhage, facial nerve palsy, brachial plexus injury and fractures. Paired cord blood gases will be taken routinely to measure arterial and venous pH and base excess. Arterial pH below 7.10 and base excess greater than −12.0 mmol/l will be used as the threshold to define significant fetal acidosis.

Secondary maternal outcomes will include extensive perineal tearing involving the anal sphincter (third or fourth degree tears), postpartum haemorrhage, shoulder dystocia, and length of postnatal hospital stay. Primary post partum haemorrhage is defined as an estimated blood loss at delivery and in the first 24 hours of more than 500mls. Postnatal stay will be considered prolonged if more than 3 days’ duration. Maternal and neonatal complications will be defined clinically according to the attending clinicians.

Procedural issues will be recorded in terms of place of delivery, need for senior obstetric support, transfer to theatre, use of sequential instruments, failure of instrumental delivery or proceeding directly to caesarean section and the decision to delivery interval.

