### The primary outcome is to compare the incidence of incorrect diagnosis of the fetal head position

The secondary outcomes are:

to compare the incidence of neonatal trauma, low Apgar scores, fetal acidosis or admission to the neonatal unit

to compare the incidence of primary postpartum haemorrhage, third and fourth degree perineal tears or prolonged postnatal admission

to compare the incidence of sequential use of instruments, instrumental delivery with more than one operator, failed instrumental delivery, transfer to theatre or caesarean section

to compare the decision-delivery intervals

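### The base-excess inequality in the fetal acidosis definition points the wrong way as written, and the rule does not say whether both criteria are required

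*Protocol article*

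**What the plan says.** The aims and objectives of the Protocol article name fetal acidosis among the secondary outcomes: "to compare the incidence of neonatal trauma, low Apgar scores, fetal acidosis or admission to the neonatal unit". That list gives no threshold.

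The threshold appears once, under Secondary outcomes. The neonatal outcomes there include "low Apgar scores, low arterial blood gases and admission to the neonatal intensive care unit (NICU". On measurement, the section says "Paired cord blood gases will be taken routinely to measure arterial and venous pH and base excess". The rule itself begins "Arterial pH below 7.10 and base excess greater than −12.0 mmol/l", and its base-excess half reads in full "base excess greater than −12.0 mmol/l will be used as the threshold to define significant fetal acidosis".

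No other part of the article defines the outcome, mentions base deficit, or says that base excess is to be taken as an absolute value. Under Statistical analysis, secondary outcomes are to be handled like the primary one, with logistic or linear regression, so a yes/no acidosis variable has to be derived from this rule.

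**The concern.** The rule names a signed quantity, attaches a minus sign to the cut-off, and then asks for values above it. Acidosis with a marked base deficit lies below −12.0, not above. The pH half of the same sentence correctly uses the low side, and the section describes the adverse blood-gas finding as low. The base-excess half contradicts both.

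What is at stake is the content of a named secondary outcome. Someone deriving the variable from recorded signed values, line by line from the text, would get a case set that leaves out infants the outcome is meant to capture and includes infants it is not. Blinding the analysis to group, as the article plans, would not expose this, because the fault lies in the case definition and not in the allocation.

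**Working it through.** No stated figure has to be reproduced. The check is whether the rule, applied as written, selects the infants it describes.

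**Inputs**, all from Secondary outcomes:
- pH criterion: arterial pH < 7.10.
- Base-excess (BE) criterion as written: BE > −12.0 mmol/l.
- Quantity recorded: base excess, signed.
- The two criteria are joined by *and*, with no statement on whether both are needed.

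**Step 1: the inequality alone.** −16 > −12 is false, so a marked deficit fails the criterion. −5 > −12 is true, so a smaller deficit meets it.

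**Step 2: the rule on example values.** *Written* uses BE > −12.0; *turned* uses BE < −12.0. *Both* requires pH and BE together; *either* accepts one of them.

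| pH | BE | Written, both | Turned, both | Written, either | Turned, either |
|---|---|---|---|---|---|
| 7.05 | −18 | no | yes | yes | yes |
| 7.05 | −14 | no | yes | yes | yes |
| 7.05 | −12.1 | no | yes | yes | yes |
| 7.05 | −12.0 | no | no | yes | yes |
| 7.05 | −11.9 | yes | no | yes | yes |
| 7.05 | −8 | yes | no | yes | yes |
| 7.05 | −2 | yes | no | yes | yes |
| 7.20 | −18 | no | no | no | yes |
| 7.20 | −14 | no | no | no | yes |
| 7.20 | −12.1 | no | no | no | yes |
| 7.20 | −12.0 | no | no | no | no |
| 7.20 | −11.9 | no | no | yes | no |
| 7.20 | −8 | no | no | yes | no |
| 7.20 | −2 | no | no | yes | no |

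**Step 3: reading the table.**
- Both required: the written and turned rules disagree for infants with pH below 7.10 at every BE except exactly −12.0, which neither strict inequality counts. They agree for infants with pH 7.10 or above, none of whom is a case.
- Either sufficient: the rules agree for infants with pH below 7.10, who all qualify through pH. They disagree for infants with pH 7.10 or above, again except at exactly −12.0. As written, the only non-cases would be infants with pH 7.10 or above and BE of −12.0 or lower.

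The two readings misplace different infants, but the base-excess clause points the wrong way in both.

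**The case against.** The strongest reply is that this is a slip of wording with an obvious intent. *Greater* was probably meant as magnitude, many clinicians would read it so, and the section's own references to low blood gases and to significant acidosis show the direction. Nothing in the article shows that the sentence was, or will be, coded literally. The raw values are recorded, so the variable can be re-derived at any time. All of this stands, and it limits the severity. It does not make the sentence right: the only definition of the outcome should not depend on the reader reversing an inequality. Nor is this detail that an article leaves to a fuller document, because the article states the threshold and states it wrongly.

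A reader might infer more than the article supports:
- *That every infant with pH below 7.10 is misclassified.* This needs both criteria to be required, which the article does not say, and it fails at BE exactly −12.0.
- *That the written rule picks out well infants.* With both criteria required, every infant counted still has arterial pH below 7.10.
- *That a harm signal would be missed or reversed.* The article gives no acidosis rate, base-excess distribution or expected difference between arms, so neither the size nor the direction of any distortion can be derived.
- *That a safety endpoint is compromised.* The article calls this a secondary neonatal outcome. Acidosis is not among the serious adverse events listed under Safety considerations, and no stopping rule is tied to it.
- *That the aims section repeats the error.* It only names the outcome.

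**Conclusion.** Wrong as written, of moderate severity. The base-excess clause selects the opposite side of −12.0 from the one that the outcome's name and the rest of the section require, whether the criteria are read as joint or as alternatives. With both required, the error falls on infants with pH below 7.10; with either sufficient, on those with pH 7.10 or above.

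The conclusion rests on two things: base excess is recorded with its sign, as the minus sign in the threshold indicates, and the rule is applied literally. If the analysts silently read it as magnitude, the derived variable would have the right direction, although the question of one criterion or both would remain open. The number of infants affected cannot be given from the article. The primary outcome, its analysis and the sample size do not depend on this rule.

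**What to change.** Replace the base-excess clause with *base excess below (more negative than) −12.0 mmol/l*, or equivalently *base deficit greater than 12.0 mmol/l*. In the same sentence, state whether an infant must meet both the pH and the base-excess criterion or only one; the present wording does not settle this, and turning the inequality alone would leave it open. Then derive the variable from the recorded cord gases with that rule, and check the code on a few pairs from the table, such as pH 7.05 with −18 and −2, and pH 7.20 with −18 and −2.

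The cost is a revised sentence and a short code check. The gases are already taken routinely, so no new data, visits or participants are needed, and recruitment, randomisation and power are unchanged.
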